
### Justification of sample size

Given the hierarchical nature of the data (i.e., the three measurement occasions at level 1 were considered to be nested within the participant at level 2), the optimal design program for power estimation of hierarchical linear models [45] was used. With three measurement occasions, three groups, and a small to moderate effect size (0.40), a total of 207 participants (i.e., 67 parents per condition) were needed to show significant differences over time. Inclusive of a potential 25% attrition rate, the total sample size required is 240.

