**Methods/design:**

The three-arm, parallel design, single-blind, randomized controlled trial will compare a team sport condition, an individual sport condition, and a “personal time” control condition over 3 months. Parents are eligible if they have a child under 13 years of age, are not participating in a sport at baseline, and are not meeting Canadian Physical Activity Guidelines. Psychosocial variables (quality of life, relationship satisfaction, social functioning, parental stress, and enjoyment) will be assessed at baseline, 6 weeks, and 3 months. A total of 161 parents have been recruited thus far from the Greater Victoria region in British Columbia, Canada. The study is ongoing with a target goal of 240 participants and an anticipated completion date of December 2021.

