## Results

To date, we have obtained ethical approval, registered the trial, and recruited 161 parents from the Greater Victoria region. Ethical approval was received from the University of Victoria Human Research Ethics Board (HREB). Of the 200 parents assessed for eligibility, 22 are currently on the wait-list for the next wave, 161 have completed all of the baseline measures, 127 have completed the 6-week measures, and 109 have completed the 3-month measures concluding the study. *See* Fig. 2 for the participant flowchart.

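### The sample-size figures contradict each other: 3 × 67 is 201, not 207, and 240 enrolled with 25% attrition leaves 180, short of either figure

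*Protocol article*

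**What the plan says.** The section Justification of sample size describes a power calculation for a hierarchical linear model with three measurement occasions, three groups and an effect size of 0.40. It concludes that "a total of 207 participants (i.e., 67 parents per condition) were needed to show significant differences over time". The next sentence makes the allowance for loss: "Inclusive of a potential 25% attrition rate, the total sample size required is 240".

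The abstract repeats the enrolment figure as the operative target: "The study is ongoing with a target goal of 240 participants". The section Randomization, allocation, and blinding fixes allocation at 1:1:1.

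**The concern.** Two adjacent sentences give four figures: a total need, a need per arm, an attrition rate and an enrolment target. The total need does not equal three times the need per arm, although the text presents them as the same number. The target does not follow from either of them at the stated attrition.

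The second mismatch matters more. A reader will take the trial to be sized to detect 0.40 after losing a quarter of its participants. On its own figures it is not. A null result on the primary comparison would then be read against a sensitivity the trial does not have.

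**Working it through.** **Inputs.** From Justification of sample size: total need 207; need per arm 67; three groups; effect size 0.40; attrition 25%; enrolment 240. From Randomization, allocation, and blinding: 1:1:1 allocation. The section gives no alpha, power, variance components or effect-size metric, so 207 itself cannot be re-derived. The check covers only whether the printed figures agree with each other.

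**Step 1: total against per-arm need.**
- 3 × 67 = 201
- 207 / 3 = 69
- The gap is 6 participants (6 / 207 = 2.9%). Equal allocation rules out unequal arms as the explanation.

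**Step 2: trying to reproduce 240.** The usual inflation is n / (1 − d) with d = 0.25; the common shortcut is n × (1 + d).

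| Base | n / 0.75 | n × 1.25 (rounded up) | Stated |
|---|---|---|---|
| 201 | 268 | 252 | 240 |
| 207 | 276 | 259 | 240 |

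Rounding up within each arm gives 67 / 0.75 → 90 per arm (270) and 69 / 0.75 = 92 per arm (276). No route gives 240. Against n / 0.75, the target is 28 to 36 participants too low.

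**Step 3: working back from 240.**
- 240 × 0.75 = 180, or 60 per arm
- 201 − 180 = 21 short; 207 − 180 = 27 short
- Attrition that 240 can absorb: 1 − 201/240 = 16.25%; 1 − 207/240 = 13.75%
- 240 fits 25% attrition only from a base of 180 (240 × 0.75), or of 192 with the shortcut (240 / 1.25). Neither base appears in the protocol.

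**Step 4: what the shortfall costs.** With everything else fixed, the detectable effect scales with 1/√n, whatever power was planned:
- 0.40 × √(67/60) = 0.423
- 0.40 × √(69/60) = 0.429

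Power at the original effect needs assumptions the protocol does not supply: two-sided alpha 0.05, a normal approximation for a two-arm comparison, and a planned power of 80% or 90% at the stated need. Power with 60 per arm is then Φ[(1.960 + z) × √(60/n₀) − 1.960], where z = 0.842 for 80% and 1.282 for 90%.

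| Need per arm (n₀) | Planned 80% | Planned 90% |
|---|---|---|
| 67 | 75.5% | 86.6% |
| 69 | 74.3% | 85.6% |

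The follow-up counts in the Results section (161 at baseline, 109 at 3 months) are not used. The trial was still running and the counts do not separate dropouts from participants not yet due, so they do not give an attrition rate.

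**The case against.** The protocol calls 25% a potential rate. If actual loss stays at or below about 14% to 16%, 240 is enough. That is correct, so the shortfall must be tied to the protocol's own 25% and not stated as certain.

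The planned analysis is a random-intercept model over three occasions, with imputation to be decided. A participant lost after week 6 still contributes two measurements. Counting only 180 completers is therefore a worst case for information, and the effect and power figures in step 4 should be read that way. This softens the consequence but does not repair the calculation: the sponsor chose to inflate for attrition, and the inflation does not give the printed result.

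The 201/207 discrepancy is small and may be a slip for 69 per arm or for a total of 201. That also stands. The attrition step is the substantive error, and it fails from either base.

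Finally, the full protocol may give alpha, power and variance assumptions. Those could explain 207, but they could not make 67 × 3 equal 207, or make 240 the result of adding 25% attrition to 201 or 207.

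**Conclusion.** The concern holds. The per-arm and total needs contradict each other by 6 participants. The target of 240 does not follow from 25% attrition on either base, under either inflation convention. At the stated attrition the trial would retain 180 participants (60 per arm), 21 to 27 fewer than it says it needs.

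The arithmetic rests only on printed figures and equal allocation. The consequence is moderate: a detectable effect of about 0.42–0.43 instead of 0.40, on completers only and with root-n scaling. Under the assumptions in step 4, power at 0.40 would be about 74–76% against a planned 80%, or about 86–87% against a planned 90%. The text must be corrected because it is the trial's stated justification for its size.

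**What to change.** Correct Justification of sample size as follows:

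1. State whether the requirement before attrition is 201 (67 per arm) or 207 (69 per arm), from the original software output.
2. Keep 240 and choose one consistent statement. Either 240 enrolled with 25% attrition gives 180 completers (60 per arm), with a detectable effect of about 0.42–0.43 at the planned power; or 240 meets the stated need only if attrition is no more than 16.25% (need 201) or 13.75% (need 207).
3. Note that 25% attrition would have required 268 to 276 enrolled.

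The 0.42–0.43 is a hand-scaled figure. Rerunning the named software with 60 per arm would confirm it. Recruitment was still open at 161 of 240, so the sponsor could instead raise the target, but the correction does not depend on that.

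The cost is a wording change here and wherever the same justification is repeated. The stated detectable effect, or the tolerated attrition, becomes slightly less favourable.

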### Intervention description, schedule, procedures, and protocol

After interested participants are deemed eligible and enrolled, they are booked for a baseline meeting. At this meeting, informed consent is obtained by a research assistant, then participants are asked to complete a baseline questionnaire containing demographic, sports commitment/behavior, and quality of life items (*see* Fig. 1 for enrollment schedule). Next, participants are randomized to one of three conditions. A research assistant who is blind to each participant’s condition presents the participant with a prepackaged envelope that reveals the condition allocation. The research assistant then outlines possible activity options and provides resources to facilitate registration in an activity program when required. Condition allocation will not require alteration of usual care pathways (including use of any medication), and these will continue for all trial arms.

Participants in the control condition are asked to use the honorarium funds to treat themselves to a weekly “night out” or “personal time” of their choice, as long as the time is not physically active and the time is spent away from their children. Examples of personal time are provided, such as going for coffee, going to the movies, or taking a workshop or class. Participants in the personal time control condition are told they will not receive any further contact until the next assessment period.

Participants in the team sport choice condition are asked to make a selection from a customized and up-to-date handout of the environmental scan of the available adult team sport programs in Greater Victoria. Participants in the team sport condition are instructed that their team sport choice must follow the basic definition set forth by Eime and colleagues [27], in which at least two participants are active in a necessary collaboration to achieve the objective of the physical activity within a set of rules. These include but are not limited to basketball, soccer, volleyball, dragon boating, and so forth. However, due to the limited nature of team sport seasons, options were somewhat constrained, depending on the time of year. Therefore, to assist with retention and autonomy in terms of choice, the criteria for team sport was slightly adapted and expanded to include registered programs that meet weekly with the same group, such as kickboxing classes, running groups, and bootcamps.

Finally, participants in the individual sport choice condition are provided with a customized handout of our environmental scan of available adult individual sports programs in Greater Victoria (maintained and updated) and asked to choose one of these available options. “Individual sport” is defined as a physical activity performed or completed by an individual with a structured rule set of competition or progression toward an outcome or goal. Individual sports include rowing, running, cycling, swimming, and rock climbing.

Upon allocation, participants are asked to begin their activity as soon as possible (i.e., register for a team sport, choose an individual sport or “personal time” activity, and commence weekly sessions). Participants in both sport conditions are asked to keep track of their attendance in the program. After the initial 6 weeks, participants are sent follow-up questionnaires to complete via email. Contact is made initially with a phone call by the research assistant to answer any questions the participants may have about their experiences over the last 6 weeks. A phone-assisted report of sport participation over the past 6 weeks is also ascertained at this time. A similar protocol is followed at the 3-month mark; however, participants are asked to come to the laboratory to partake in a brief wrap-up interview and an end-of-trial questionnaire (*see* Fig. 1 for schedule of interventions and assessments). To assist study retention, we offer to subsidize the program chosen by participants with a maximum $80 contribution toward registration (or the personal time activity of choice for the control participants) as well as a maximum $25-per-week contribution toward childcare when needed. Participants must complete the study in order to receive the honorarium.

## Results

To date, we have obtained ethical approval, registered the trial, and recruited 161 parents from the Greater Victoria region. Ethical approval was received from the University of Victoria Human Research Ethics Board (HREB). Of the 200 parents assessed for eligibility, 22 are currently on the wait-list for the next wave, 161 have completed all of the baseline measures, 127 have completed the 6-week measures, and 109 have completed the 3-month measures concluding the study. *See* Fig. 2 for the participant flowchart.

**Fig. 2 Fig2:**
[figure not shown]
Participant flow diagram

### Oversight, monitoring, ethics, and dissemination

#### Oversight and monitoring

Because of the relative simplicity of the data collection methods, the research team concluded that a formal data monitoring committee was not required. As an alternative, the project coordinator provides a monthly report of trial progress, including advances toward intended sample size and the quality of the data collected. The principal investigator is responsible for project oversight, will make the final decision to terminate the trial, and will have access to the final trial dataset.

#### Research ethics processes

In the case of any protocol changes, the project coordinator submits the appropriate documentation to the ethics board (HREB at the University of Victoria) to request modifications or amendments. Upon approval, any amendments are communicated to relevant parties, and the trial registry is updated accordingly.

It is anticipated that there will be no harms as a result of participation; nevertheless, participants are provided with contact information for the project coordinator, primary investigator, and HREB in the case of unintended effects or adverse events. All those involved in study implementation are trained to document and report any such events. If such an event occurs, depending on its nature, the safety of all parties involved will be ensured.

#### Dissemination plans

Results of this trial will be widely disseminated through knowledge exchange activities, including presentations at relevant scholarly conferences and publications in scientific journals. All those who have contributed to the design and protocol will be eligible for authorship of subsequent publications. Findings may have important implications for public health and could potentially inform initiatives for adult sport participation. Public access to the participant data set will not be granted. Currently, there are no plans to make the statistical code publicly available (as per our HREB approval). Any relevant publications will be shared with participants who have expressed interest.

## Discussion

This protocol describes the implementation of a randomized controlled trial that investigates the efficacy of two sport participation formats (individual sport and team sport) with regard to key psychosocial outcomes, based on the tenets of the Sport Participation Model, among parents with young children. Research findings will be important to public health because they may help to determine whether sport participation among parents improves psychological health and physical activity participation. Because little empirical evidence of the effect of sport participation among this demographic exists, this information could prove pivotal for policy-level sport interventions geared toward promoting positive psychosocial outcomes for parents.

## Trial status

The protocol (version 2) was updated with the National Library of Medicine on October 10, 2019. Recruitment for this trial started in September 2016 when version 1 of the protocol was initially released. We aim to complete recruitment by December 2021. The study is ongoing as of February 2020, and data analysis will continue through 2022.

## Data Availability

The datasets generated and/or analyzed during the current study are not publicly available as per ethical approval from the HREB at the University of Victoria, which stipulates that the data will not be accessed or analyzed by others.

## Abbreviations

CSEP: Canadian Society for Exercise Physiology
HREB: Human Research Ethics Board at the University of Victoria
PA: Physical activity
SF-12: 12-Item Short Form Health Survey
